### Interventions

Included in this study are 2 interventions: 1) PM training intervention (Virtual Week Training Program) and 2) the active control intervention (non-adaptively difficult word puzzles). The active control intervention is active in the sense that participants undergo an intervention that they may perceive as a plausible technique for improving cognition, but which is not evidenced to do so, similar to a placebo control. Relative to a passive control, such as usual care in a medical context, an active control is a more rigorous test of the effects of cognitive training.

### PM training intervention - Virtual Week Training Program

HF patients randomly allocated to receive the computer-based PM training strategy (Virtual Week Training Program) will continue to receive their usual care from service providers; this may be from any combination of nurse-led chronic disease management, specialised HF outpatient clinics, or outpatient rehabilitation programs. As a supplement to usual care, the Virtual Week Training Program intervention will have all the critical features of a restorative training task with lots of repetition and adaptive difficulty whereby the task starts at a relatively easy level and then progressively becomes more difficult, adapting to the performance level achieved by the participant. A key feature of this program is the distributed practice of the cognitive training, in this case over 6 weeks, rather than massed practice in 1 or 2 long sessions. Another training feature is that the Virtual Week Training Program provides feedback at the conclusion of each ‘virtual day’ (which will occur twice per session), so that participants are aware of their performance on each day and of their progression through the difficulty levels. Previous training tasks have mixed success with often low levels of far transfer, and this is arguably because the training tasks have not been specifically targeted towards desirable outcome behaviours. We have developed ‘virtual days’ that mimic many of the daily tasks HF patients would be expected to follow in real life. For example, when patients participate in the Virtual Week Training Program, they are asked to simulate activities like weighing themselves daily in the morning, evaluating their HF symptoms in the evening, and assessing their fluid intake at several times during the day. In addition, there are event-based tasks that involve exercise. Therefore, the Virtual Week Training Program is more related to PM than many previous restorative training programs that train performance on basic cognitive tasks, such as working memory [33].

The Virtual Week Training Program has been substantially developed since the reported pilot [33]. The number of ‘virtual days’ has been doubled and each of the 48 days contains a different set of event cards to simulate unique sets of daily activities and PM tasks. This avoids the repetition of ‘virtual days’ that was needed in the pilot and extends the sessions from 12 sessions over 4 weeks to 24 sessions over 6 weeks. The training program is now fully automated so that participants can complete the training sessions in their own homes without needing to travel to the laboratory for supervised administration.

The research assistant conducting the training sessions will be blinded to baseline assessments. It is anticipated that the first training session will take 40 to 45 minutes where the patient will be provided with a USB version of the Virtual Week Training Program to use on their home computer over 6 weeks. Patients will be instructed to use the training program 4 times per week over 6 weeks. Each training session will take approximately 20 to 30 minutes to complete. On insertion of the flash drive into the patient’s computer, prompts will initiate the training at the appropriate level and limit the number of ‘virtual days’ (2) that can be completed in 1 session and the number of sessions that can be completed on each actual day (1) and each actual week (4). The Virtual Week Training Program records all responses, scores multiple measures of performance, and uploads the data to the experimenter’s database at the completion of each session so that the patient’s progress can be monitored. Face-to-face support will be arranged where needed.

### Active control group - puzzle training

To determine whether cognitive training has any additional health benefits for HF patients there will be an active control group to enable comparisons of outcome measures between the two HF groups. HF patients randomly allocated to the active control will continue to receive their usual care from service providers; this may be from any combination of nurse-led chronic disease management, specialised HF outpatient clinics, or outpatient rehabilitation programs. This condition will involve participants completing computerised word puzzles, and will be presented not as a control activity but as a plausible training activity. This particular control has been implemented due to the widespread belief that ‘brain teasers’ (for example, crossword puzzles) help with brain fitness, yet evidence for the efficacy of commercial brain-training exercises is limited [70].

To control for the social and participatory features of the PM training, patient participants in the control group will be asked to complete a set of word puzzles for a similar amount of time to the restorative memory training condition. That is, they will be asked to spend 20 to 30 minutes per day completing a set of word puzzles, 4 times per week, over 6 weeks. The key distinguishing features of the word puzzles compared to the Virtual Week Training Program is that the puzzle difficulty is manageable and non-adaptive. Compared to the PM training group, patient participants in the control group will have similar levels of contact with the research assistant: the introductory sessions will be conducted face-to-face to introduce them to the puzzle training; subsequent telephone contact twice a week to support and monitor their participation in the puzzle training. Patient participants will be given specific instructions and support to Email screenshots to the research assistant to monitor their participation and progress.

### Randomisation and allocation concealment

Using CONSORT principles [71] HF patients will be randomised to 1 of the 2 study interventions: 1) usual care plus PM training (see Figure 1) or 2) active control group. Block randomisation will be allocated via a computer generated number prepared by an investigator with no involvement in data collection. Block randomisation with 1:1 ratio will be used to keep the 2 groups at similar sizes. Once the HF patient has consented to the study and baseline measures have been collected the research assistant will contact one of the training study investigators, who are independent of the recruitment process and data collection, for allocation consignment. Research assistants collecting baseline measures will not be informed of the patient’s assignment. Instead, the research assistant conducting the cognitive training will be notified when a patient has been randomised to this intervention. Participants enrolled in the study will be aware of the training activity they have been allocated and therefore they will not be blinded to the treatment allocation.

**Figure 1 Fig1:**
[figure not shown]
Consolidated Standards of Reporting Trials (CONSORT) diagram illustrating study procedures. Key: BNP, brain natriuretic peptide; CAS-R, Control Attitudes Scale - Revised; CC-SCHFI, Caregiver Contribution Self-Care Heart Failure Index; CRA, Caregiver Reaction Assessment; Dyadic HF Typology, Dyadic Heart Failure Typology; HADS, Hospital Anxiety and Depression Scale; Heart-FaST, Heart Failure Self-care Screening Tool; HF, heart failure; MIST, Memory for Intentions Screening Test; MCSI, Modified Caregiver Strain Index; MoCA, Montreal Cognitive Assessment; NP-battery test, Neuropsychological battery test; Proxy IADL, Proxy measure Instrumental Activities of Daily Living; SCHFI, Self-Care Heart Failure Index; TIADL, Timed Activities of Daily Living.

The study has received ethical approval from the St Vincent’s Hospital, Melbourne (HREC-A 018/14) and Australian Catholic University (Ethics Register Number: 2014 175 V) Human Research Ethics Committees and will conform to the principles outlined in the *Declaration of Helsinki* and to the Consolidated Standards of Reporting Trials (CONSORT) guidelines for a randomised controlled study comparing the efficacy of two non-pharmacological health interventions [72]. The trial is registered with the Australian New Zealand Clinical Trials Registry (ANCTR: reference number #366376). All subjects will provide written informed consent to participate in the study.

### Sample size

Based on data from other relevant trials of patient education and HF self-care, an eight-point difference in standardised self-care scores is a clinically important change [73]. Using the G*power calculator it was estimated that in order to achieve an 80% power at a 0.05 significance, a sample size of 63 per group is required to detect a small to medium effect of the self-care intervention on hospitalisations [73]. Using analysis of covariance (ANCOVA) to examine for clinically significant differences in standardised self-care maintenance and management scores between the 2 HF groups, a total of 100 patients in each group (200 in total) will have > 90% power (α of 0.05) to detect a medium effect size (f^2^ = 0.4) in the primary endpoint. The probable requirement to undertake non-parametric statistical analyses (due to non-Gaussian distributed data) has been factored into study power calculations in addition to a 20% intervention refusal rate and loss to follow-up. The sample size for the comparison of baseline cognitive performance (in particular PM) between 60 HF patients and a healthy age-matched control group has been based on previous studies [55,74]. As such, the sample size has the power to detect significant differences with moderate effect sizes.

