### Statistical analyses

To compare and confirm cognitive deficits, including PM, between HF patients and a healthy matched control, group differences in baseline PM and neuropsychological tests will be examined using inferential statistics (*t*-test and analysis of variance; ANOVA). To analyse the changes in each measure assessed at each time point (baseline, Assessment One and Assessment Two) we will use separate mixed ANOVAs for all dependent variables. The within-groups variable will be *testing phase* (baseline, Assessment One, Assessment Two) and the between-groups variable will be *Training group* (PM training, word puzzles). Multiple regression analysis will be performed to identify whether physical, cognitive, emotional and mental functioning variables are independent predictors of HF self-care and consulting behaviours, after adjusting for clinical characteristics. For all analyses, α levels will be set at 0.05 and effects sizes will refer to partial η-square values.

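### The effect size in the primary power statement (f² = 0.4, called medium) is d = 1.26 for two groups, cannot have produced 200 patients, and is not tied to the eight-point difference

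*Protocol article*

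**What the plan says.** All of this stands in the Sample size section of the protocol article.

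- The clinical target: "an eight-point difference in standardised self-care scores is a clinically important change". No SD accompanies it.
- The primary calculation uses ANCOVA on the self-care maintenance and management scores, with 100 per arm. The claim is that this number "will have > 90% power (α of 0.05) to detect a medium effect size (f^2^ = 0.4) in the primary endpoint".
- Allowances: non-parametric analysis is said to be built into the power calculations already, "in addition to a 20% intervention refusal rate and loss to follow-up".
- A separate calculation concerns a different outcome: "a sample size of 63 per group is required to detect a small to medium effect of the self-care intervention on hospitalisations".

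The Study design section gives 200 as the number randomised. The Statistical analyses section adds "For all analyses, α levels will be set at 0.05". Neither section states whether tests are one- or two-sided.

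**The concern.** In a two-group comparison, f² and the standardised difference d are tied by a fixed formula, so the stated value can be checked against its label and against the sample size it is meant to support. It fits neither. A reader cannot tell which effect the trial was sized to detect.

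The eight-point difference is the natural anchor, but without an SD it enters no calculation. The power to detect what the investigators call clinically important is therefore not stated anywhere in the article. The claim that loss and non-parametric testing are already allowed for cannot be checked either, since the answer depends on which effect size was really used.

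**Working it through.** **Inputs from the article.** α = 0.05; 1:1 allocation; 200 randomised; f² = 0.4; power above 90%; 20% refusal and loss; eight points.

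**Assumptions, not in the article.** Two-sided test; one covariate; the 20% taken as one overall loss, so 200 × 0.8 = 160 analysed; rank-test efficiency 0.955 (the value for normal data).

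**Formulas.** For two equal groups f = d/2, so d = 2√(f²). Power is that of a noncentral F test with 1 and N − 3 degrees of freedom and noncentrality λ = f² × N.

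**1. The stated figure.** f² = 0.4 gives f = 0.632 and d = 1.26. With N = 200, λ = 80; with N = 160, λ = 64. Power exceeds 99.99% in both cases, so the bound of more than 90% is literally met. Working backwards, 90% power is reached at N = 29 in total (29/0.8, rounded up, is 37 randomised).

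**2. If the exponent is a slip.** f = 0.4 gives f² = 0.16 and d = 0.8. Power is 99.99% at 200 and 99.9% at 160; 90% needs N = 68 (85 randomised).

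**3. If a conventional medium effect was meant.** f = 0.25, f² = 0.0625, d = 0.5, with no covariate gain:

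| Analysed | λ | Power |
|---|---|---|
| 200 | 12.5 | 94.0% |
| 160 (20% loss) | 10.0 | 88.2% |
| 153 (160 × 0.955) | 9.6 | 86.7% |

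90% needs 171 analysed, or 171/0.8 ≈ 214 randomised.

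**4. Credit for the covariate.** If d = 0.5 is expressed on the raw SD and the baseline covariate correlates r with the outcome, f² becomes 0.0625/(1 − r²).

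| r | Power at 160 | Power at 153 |
|---|---|---|
| 0 | 88.2% | 86.7% |
| 0.25 | 90.1% | 88.8% |
| 0.30 | 90.9% | 89.6% |
| 0.35 | 91.9% | 90.7% |
| 0.50 | 95.3% | 94.4% |

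**5. Link to eight points.** SD = 8/d. The SD implied by f² = 0.4 is 6.3 points, by f = 0.4 it is 10, and by f = 0.25 it is 16, on a scale of 100 points. For a range of assumed SDs with no covariate gain:

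| SD | d | Power at 200 | Power at 160 |
|---|---|---|---|
| 15 | 0.53 | 96.3% | 91.8% |
| 16 | 0.50 | 94.0% | 88.2% |
| 18 | 0.44 | 87.8% | 79.8% |
| 20 | 0.40 | 80.4% | 71.0% |

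**The case against.** Several replies have force.

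- **The value is legitimate and the bound is true.** f² can be any number from zero upwards, so 0.4 is not an impossible value. With it, power exceeds 90% even at 160 analysed. Both points stand, but neither makes 0.4 a medium effect nor explains why 200 patients are needed.
- **A power shortfall is not shown.** A reader might infer that the trial misses 90% once its own 20% loss is applied. That needs f = 0.25 to be put in place of the stated value, and it needs ANCOVA to gain nothing from its covariate. The gap at 160 is then 1.8 points. A correlation of about 0.25 closes it (0.30 to 0.35 with the rank allowance). A one-sided test would give 93.5%, and f² = 0.15, the medium value for regression, gives 99.8%. This stands: the shortfall is conditional.
- **The 63-per-group figure may be right as written.** It is tempting to call it a mislabelled calculation for means with d = 0.5. But a 1-df chi-square test with w = 0.25, between the conventional small (0.1) and medium (0.3) values, needs exactly 126 patients (63 per group) for 80% power: 79.8% at 125 and 80.1% at 126. That suits an outcome analysed as a proportion, such as hospitalisation. The test is not named, so an error is not established.
- **A null result would still be readable.** It would be judged by the estimate and its confidence interval against eight points, not by the planning effect size. This also stands.
- **An article may leave the SD and the correlation to the full protocol.** That is fair for an omission. It does not cover an effect size that is stated and labelled wrongly.

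**Conclusion.** The effect size in the primary power statement is wrong as labelled. On the literal reading it is d = 1.26, on the most charitable reading of the symbol d = 0.8, and neither leads to 200 patients (29 or 68 would give 90% power). This rests only on the two-group conversion and a two-sided 5% test. The missing SD leaves the statement unconnected to the eight-point target.

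What the design delivers for a conventional medium effect is conditional: 94% with 200 analysed, about 88% with 160, and about 87% with the rank allowance, all without covariate gain. At 160 it reaches 90% if the baseline correlation is about 0.25 or more. The documents therefore support neither a claim that the trial is underpowered nor one that its 63-per-group hospitalisation figure is mistaken. This is a wrong input to be corrected, not a case for a larger trial.

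**What to change.** Rewrite the primary power statement and keep 200 randomised.

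1. Delete f² = 0.4.
2. State the effect in one correct metric, tied to eight points and an assumed SD with its source. For example, eight points with SD 16 is d = 0.5, f = 0.25, f² = 0.0625.
3. Give power at the 160 evaluable patients: about 88% for d = 0.5 (about 87% with a rank-based test) without covariate gain, or above 90% with the credited baseline correlation stated.
4. Say whether the test is two-sided and how large the non-parametric allowance is.

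Leave the 63-per-group hospitalisation figure out of this correction.

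The cost is one reworded paragraph and a stated power that may become slightly less favourable. No patients, visits or analyses are added.

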**Methods/design:**

The proposed study is a randomised, controlled trial in which 200 patients diagnosed with HF, and their carers will be recruited from 3 major hospitals across Melbourne. Eligible patients with HF will be randomised to receive either: 1) The Virtual Week Training Program - a computerised prospective memory (PM) training program (intervention) or 2) non-adaptive computer-based word puzzles (active control). HF patients’ baseline cognitive function will be compared to a healthy control group (n = 60) living independently in the community. Patients will undergo a comprehensive assessment of PM, neuropsychological functioning, self-care, physical, and emotional functioning. Assessments will take place at baseline, 4 weeks and 12 months following intervention. Carers will complete measures assessing quality of life, strain, perceived control in the management of the patients’ HF symptoms, and ratings of the patients’ level of engagement in HF self-care behaviours.

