## Methods/design

### Study design

This will be a randomised controlled trial where 200 patients with HF will be randomised to receive either: 1) the Virtual Week Training Program, a computerised adaptively difficult PM training program, or 2) non-adaptive computer-based word puzzles. Sixty healthy control participants, with no HF diagnosis, will also be assessed to compare differences in baseline measures of cognitive and psychosocial functioning. There are 4 phases to the study: 1) baseline testing; 2) 6 weeks of cognitive training; 3) Assessment One, 2 to 4 weeks post cognitive training; and 4) Assessment Two, 12 months post cognitive training. There will be two separate interviews during each of the assessments (baseline testing, Assessment One and Assessment Two). These will be: a) nursing assessment including physical functioning, and self-care; and b) PM and neurocognitive assessment, and TIADL.

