### Participant inclusion criteria

A total of 200 HF patients aged 18 years or older will be recruited. Inclusion criteria will be: diagnosis of HF with reduced ejection fraction (ejection fraction < 45% in the previous 2 years) as confirmed by a cardiologist and consistent with Australian guidelines [34]; attendance at a specialist HF clinic or rehabilitation program, and/or a disease management program with nursing follow-up and able to participate in the study (that is adequate vision, hearing and English comprehension). Carers will be identified by HF patients as someone who is familiar with and contributes to the management of their heart condition (for example, a partner, family member, friend or next of kin). Patients who cannot identify a carer will still be eligible to participate in the study. All HF patients enrolled in the study will continue to receive usual care which can be from any combination of nurse-led chronic disease management programs, specialised HF outpatient clinics, or outpatient rehabilitation programs. A key aspect of usual care is patient education and support from a multidisciplinary team that is directed at promoting self-care maintenance and monitoring behaviours. Healthy control participants will be living independently in the community without a medical diagnosis of HF and have adequate performance on the Addenbrooke’s Cognitive Examination Revised (ACE-R) [35].

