### Recruitment

Participants will be recruited over a 24-month period, or until the required sample size is achieved. A HF nurse will initially assess patients’ eligibility to participate in the study: those who meet the inclusion criteria will be referred to the study research assistant who will approach potential participants at their outpatient appointment, explain the study (both verbal and written information), and obtain their consent. They will be asked to identify if they have an informal carer or next-of-kin who would be willing and able to complete some questionnaires for the study. A research assistant will contact the carer, explain the study and their involvement, obtain consent and collect baseline questionnaires. Healthy control participants will be sourced from the community by advertisements in local newspapers and word-of-mouth. Research assistants will screen control participants for study eligibility, explain the study and obtain their consent to undergo the neurocognitive testing. Healthy control participants will be matched to HF patients according to age, premorbid intelligence and gender.

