### Baseline and follow-up measures to be collected from all HF patient participants

A comprehensive baseline assessment of HF patients will be conducted prior to randomisation and the first intervention session. The baseline assessment will include socio-demographic, psychosocial, cognitive and clinical profiling using a combination of self-report and review of patient records. Table 1 displays baseline, 4-week and 12-month assessments. The following measures will be administered during the assessment:

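### The baseline heart-failure versus healthy-control comparison is sized on 60 patients but described for heart-failure patients generally, and the named tests leave out the matching factors

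*Protocol article*

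**What the plan says.** The first listed aim is to confirm cognitive deficits, including prospective memory (PM), in HF patients relative to matched healthy people.

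- **Sample size:** the size is set for the "comparison of baseline cognitive performance (in particular PM) between 60 HF patients and a healthy age-matched control group" and rests on earlier studies. The section adds that this size has power for moderate effects. It gives no effect size, standard deviation or power figure for this comparison.
- **Abstract:** HF patients' "baseline cognitive function will be compared to a healthy control group (n = 60"), with no subset of patients named.
- **Study design:** "Sixty healthy control participants, with no HF diagnosis, will also be assessed", alongside the 200 randomised patients.
- **Participant inclusion criteria:** "A total of 200 HF patients aged 18 years or older will be recruited".
- **Baseline and follow-up measures (HF patients):** "A comprehensive baseline assessment of HF patients will be conducted prior to randomisation and the first intervention session". Table 1 lists the PM tests, the neuropsychological tests and the NART at baseline for HF patients, and marks them as also collected from the controls.
- **Recruitment:** "Healthy control participants will be matched to HF patients according to age, premorbid intelligence and gender". No matching ratio or method is given.
- **Statistical analyses:** for this comparison, "group differences in baseline PM and neuropsychological tests will be examined using inferential statistics", namely the t-test and ANOVA, at an alpha of 0.05 whose sidedness is not stated.

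**The concern.** Two things do not fit together.

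**Which patients are compared.** The number 60 for the HF group appears only in the Sample size section. If it governs, up to 140 tested patients stay out of the comparison, and nothing says which 60 go in, so the choice could be made after scores are known. If instead all HF patients are compared, as the other sections read, the sizing sentence describes a different comparison from the one to be done.

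**How the matching is used.** Age, gender and NART are measured in both groups and chosen as matching factors, yet the named tests use neither pairs nor covariates. At 60 v 60 an unadjusted test gives up precision that the design paid for. With 60 controls and up to 200 patients, one-to-one matching can cover at most 60 patients, and nothing in the named analysis protects against imbalance in the rest.

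At stake are the precision and credibility of the first aim. The randomised comparison is not affected.

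**Working it through.** **Inputs.** HF patients: 60 (Sample size) or up to 200 (Participant inclusion criteria). Controls: 60 (Study design). Alpha: 0.05 (Statistical analyses), taken as two-sided, which is an assumption. Effect: the article says only *moderate*; d = 0.5 is an assumption, with 0.4 to 0.6 shown as a range. The article states no power for this comparison, so there is no figure to reproduce.

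**Standard error of the difference, in SD units:** sqrt(1/n1 + 1/n2).

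- 60 v 60: sqrt(1/60 + 1/60) = 0.1826
- 200 v 60: sqrt(1/200 + 1/60) = 0.1472
- Ratio: 0.1472/0.1826 = 0.806, so the standard error is about 19% smaller

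**Power, normal approximation:** Φ(d/SE − 1.96).

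- 60 v 60, d = 0.5: 0.5/0.1826 = 2.739; Φ(0.779) = 78.2%
- 200 v 60, d = 0.5: 0.5/0.1472 = 3.397; Φ(1.437) = 92.5%

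The noncentral t gives nearly the same results:

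| Assumed d | 60 v 60 | 200 v 60 |
|---|---|---|
| 0.4 | 58.4% | 77.3% |
| 0.5 | 77.5% | 92.3% |
| 0.6 | 90.3% | 98.2% |

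Over d = 0.4-0.6, taking both methods together, 60 v 60 runs from 58% to 91% and 200 v 60 from 77% to 98%.

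**Smallest d with 80% power (t):** 0.516 for 60 v 60; 0.414 for 200 v 60.

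**Size needed for 80% power at d = 0.5:** 2 × (1.96 + 0.842)²/0.5² = 62.8, so 63 per group (64 with the t distribution).

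**Fewer evaluable patients.** The neurocognitive assessment section makes an acceptable ACE-R result a condition for keeping a participant's data, so 200 is an upper limit. The loss is not stated. At d = 0.5 against 60 controls, 160 evaluable HF patients give 90.8% power and 120 give 88.2%.

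**Using the matching factors.** This gain is separate from the gain in numbers. If the covariates explain an assumed 10-30% of the outcome variance, d becomes 0.5/sqrt(1 − R²):

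- 60 v 60: 81.7% to 90.1%
- 200 v 60: 94.6% to 98.1%

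If 60 matched pairs were analysed as pairs, with an assumed within-pair correlation of 0.2 to 0.4, power would be 85.4% to 93.5%.

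**The case against.** - **A sizing number does not define an analysis set.** This is fair. A reader might infer that the plan discards 140 patients. The documents do not establish that: only the Sample size section names 60 HF patients, and the design and analysis text sets no such limit. What stands is the conflict and the missing selection rule.
- **The power sentence is not shown to be wrong.** This is also right. A reader might conclude that the plan admits to 78% power or misses an 80% target. It states neither a power nor a target for this comparison, and 60 v 60 reaches 80% at d = 0.52, which is still a moderate effect. The 78% and 92% belong to an assumed d = 0.5.
- **The data are not yet in hand.** Trial status says that the study is recruiting. The tests are planned for all patients, and up to 200 will be evaluable.
- **Matching already handles confounding, and covariates are often left to an analysis plan.** This stands in part. An ordinary t-test on well-matched groups tends to be conservative rather than biased. If the controls are matched to the whole HF group by frequency, balance could be acceptable at 200 v 60, but the article does not say so. It does name the tests for this comparison, and in the same section it provides adjustment for the regression on self-care but not here.
- **A matched primary analysis is defensible.** It is. Using all patients trades some comparability by design for precision, and reliance on a regression model is a real cost. Even so, a matched subset needs a selection rule fixed in advance and an analysis that uses the matching factors.
- **This is a secondary, non-randomised question.** True, and it limits the weight of the point. It remains the first listed aim.

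**Conclusion.** The point holds as an unreconciled statement of who is compared, joined to an analysis that leaves collected matching factors unused. Comparing all evaluable HF patients with adjustment is better than the method named: it is more precise, and it protects against imbalance when 60 controls face a larger patient group.

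Assuming d = 0.5 and a two-sided 0.05 level, moving from 60 to 200 HF patients raises power from about 78% to about 92%, and to about 91% if 160 are evaluable. That gain comes only from numbers, and it would be lost only if the Sample size section governs the analysis. Adjustment adds more, by an amount that depends on covariate strength, which the article does not give. The randomised comparison and the primary self-care outcomes are untouched.

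**What to change.** Reconcile the Sample size section with the Abstract, Study design and Statistical analyses sections:

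1. State that all evaluable HF patients with baseline data (up to 200) are compared with the 60 controls by linear regression or ANCOVA, adjusted for age, gender and NART.
2. Keep a 60:60 matched subset, with its selection rule fixed in advance, as a sensitivity analysis. If the matched subset is to stay primary, define its selection in advance and still adjust for the matching factors.
3. State the assumed effect size, the sidedness and the resulting power for the numbers expected after the ACE-R screen.

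The cost is wording and one regression per measure. No new data are needed, and recruitment is still open. The small downside is that, for HF patients outside the matched subset, comparability rests on covariate adjustment.
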